#### Control group

We established a QQ chat group and invited participants into this group. The same training resources as emergency preparedness training content index system and the knowledge corner are pushed to participants, and participants are required to study independently and complete online check-in for 2 weeks. Participants will be rewarded with 50 RMB after completing daily tasks and questionnaire, just like the intervention group. But this group does not have elements of storylines, virtual scenes, interactions and scoring.

### Recruitment, randomization, and allocation concealment

#### Recruitment

Participants will be recruited through both online and on-site recruitment. The sample size calculation is based on the primary outcome: emergency preparedness of public for MEIDs. The sample size was performed using the formula developed by Chow [18], and the formula is as follows:$$\begin{array}{c}\mathrm{n}=2{\left(\sigma \frac{{z}_{1-\alpha /\left(2T\right)}+{z}_{1-\beta }}{{\mu }_{A}-{\mu }_{B}}\right)}^{2}\\ 1-\beta =\varphi \left(z-{z}_{1-\alpha /\left(2T\right)}\right)+{\varphi }\left(-z-{z}_{1-\alpha /\left(2T\right)}\right), z=\frac{{\mu }_{A}-{\mu }_{B}}{\sigma \sqrt{\frac{2}{n}} }\end{array}$$

The significance level of the test is α = 0.05, the test power is 1-β = 0.8, standard deviation is = 26.31, the number of comparisons to be made is T = 3, is the standard Normal distribution function. Calculator software (Power and Sample Size) was used to calculate the initial sample size N1 = 171. Considering the attrition rate of 20%, the sample size of each group was increased to 206, and the total sample size of the three groups was 618.

The study will be conducted in Luzhou City, Sichuan Province, China. Participants were recruited from the community and signed informed consent forms if they agreed to participate in the study and complete follow-up measurements. After completing the study, each participant will receive a reward of 50 RMB in cash.

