## Methods

### Study design

The design type of this study is a randomized controlled trial. Study participants will be recruited from public volunteers and allocated to one of the three randomized groups after completing a baseline survey (Fig. 1) (The People’s War Against Pandemic intervention group 1, The People’s War Against Pandemic intervention group 2, Control group). Three follow-up visit assessments are required to complete for participants at four weeks later, three months and six months after the intervention. Our hypotheses are:There is no statistical difference between The People’s War Against Pandemic intervention group 1 and The People’s War Against Pandemic intervention group 2 in prevention and control knowledge of MEIDs and emergency preparedness of MEIDs.Comparing The People’s War Against Pandemic intervention group 1 and Control group, the former group will have better effect on improve prevention and control knowledge of MEIDs and emergency preparedness of MEIDs.Comparing The People’s War Against Pandemic intervention group 2 and Control group, the former group will have better effect on improve prevention and control knowledge of MEIDs and emergency preparedness of MEIDs.

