
### Intervention design: overview

#### The People’s War Against Pandemic intervention group 1

Participants are asked to use The People’s War Against Pandemic for a two-week intervention. Participants need to complete the storyline task at least once a day, watch at least one article and one video in the knowledge corner, and complete a retest of wrong choices in the intelligent evaluation module. Researchers check the completion of participants through the user management module, and those who fail to complete will be reminded by sending text messages or phone. The effect of the intervention will be evaluated by using the same questionnaire as applied in the baseline survey at week one and two of intervention. Before the training, participants will be informed that they will be rewarded with 50 RMB after completing daily tasks and questionnaire.

#### The People’s War Against Pandemic intervention group 2

Participants are asked to use The People’s War Against Pandemic for a four-week intervention. Other requirements are the same as those of intervention group 1. The effect of the intervention will be evaluated at week 1, 2, 3, 4 of intervention. The purpose of setting this group is to explore the optimal duration of the training, so that the participants will neither fail to achieve the training effect due to too short time nor get bored due to too long time.

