### Data management and statistical analysis

Data will be collected, recorded and managed by the Survey Star, an online questionnaire platform (www.wjx.cn, Changsha Ranxing Information Technology Co., Ltd in China) to ensures the safety, integrity and consistency of the data. Researchers will download the data from Survey Star and save it in text format to a password-protected server. SPSS 21.0 analysis software was used for data analysis by the third party who did not participate in the intervention.

Data will be collected at baseline and descriptive statistics will be used to show the characteristics of each arm at baseline. The outcome indicator prevention and control knowledge of MEIDs is a binary variable, so the chi-square test will be used to compare among the three arms at the intervention completion, 1, 3, and 6 months after the intervention. Analysis of Variance (ANOVA) will be used to find out whether there are differences among the three arms in the outcome indicator-emergency preparedness of public for MEIDs. Repeated Measures ANOVA will be used to measure weather there are differences in emergency preparedness of public for MEIDs score at 1, 3, and 6 months after intervention. A Bonferroni correction will be used for multiple testing. Intention-to-treat analysis will be used to account for the influence of attrition. The difference was statistically significant when *P* ≤ 0. 05.

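### Hypothesis 1 (2 versus 4 weeks do not differ) would be supported by a non-significant difference test, and the Bonferroni divisor of 3 makes false support more likely

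*Protocol article*

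**What the plan says.** The Study design section of the protocol article lists three hypotheses, each covering both the preparedness score and the knowledge outcome. The first opens "There is no statistical difference between" and names the 2-week and 4-week platform groups. The other two predict that each platform group does better than control.

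Under Recruitment, the sample size formula takes the normal quantile at 1 − α/(2T). The inputs are "The significance level of the test is α = 0.05, the test power is 1-β = 0.8", "standard deviation is = 26.31" and "the number of comparisons to be made is T = 3". The result is that the Power and Sample Size calculator "was used to calculate the initial sample size N1 = 171" per group, raised to 206 for 20% attrition. The difference between means is not given.

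The Data management and statistical analysis section plans chi-square tests, ANOVA and repeated measures ANOVA, all of them tests for a difference, and adds: "A Bonferroni correction will be used for multiple testing". It does not say which tests form the family.

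On the 4-week group, the Intervention design section says: "The purpose of setting this group is to explore the optimal duration of the training". The Discussion says that comparing the two platform groups will identify the best duration.

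**The concern.** A Bonferroni correction limits false claims that groups differ. Hypotheses 2 and 3 make such claims, so the correction protects them. Hypothesis 1 predicts the opposite. With no margin and no equivalence test stated, the only result in the plan that can support it is a non-significant one, and the error that falsely supports it is failing to detect a real difference. Tightening the significance level makes that error more frequent, so the adjustment favours the result that the article predicts.

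At stake is a conclusion that two weeks of training do as well as four, reached because the test could not see the difference. Counting this comparison also takes the level for the two contrasts with control from 0.025 to 0.0167. That cost is smaller and needs separate treatment.

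**Working it through.** **Inputs.** From Recruitment: α = 0.05, power 0.80, SD 26.31, T = 3, 171 per group before attrition, 206 after. Normal quantiles: z(1 − 0.05/6) = 2.394, z(1 − 0.05/4) = 2.241, z(0.975) = 1.960, z(0.80) = 0.842.

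**The plan's own figure.** The formula is n = 2[SD(z₁ + z₂)/δ]², with z₁ the quantile for α/(2T) and z₂ the quantile for power. Since δ is missing, 171 cannot be strictly reproduced, but it can be solved backwards. The standard error at 171 per arm is 26.31 × √(2/171) = 2.845, so δ = 2.845 × (2.394 + 0.842) = 9.21 points, or 0.35 SD. The 206 equals 171 × 1.2 = 205.2, rounded up. With 20% lost, 206 × 0.8 leaves about 165.

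**Chance that a real 2 versus 4 week difference is missed.** For a true difference d and critical value c, this is Φ(c − d/SE) − Φ(−c − d/SE). With SE = 2.845, the observed difference needed for significance is 1.960 × 2.845 = 5.58 points unadjusted and 2.394 × 2.845 = 6.81 points with T = 3.

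| True difference | Unadjusted 0.05 | T = 3 (0.0167) | Ratio |
|---|---|---|---|
| 3 points | 81.6% | 91.0% | 1.1 |
| 5 points | 58.0% | 73.8% | 1.3 |
| 7 points | 30.8% | 47.4% | 1.5 |
| 9.21 points (back-solved) | 10.1% | 20.0% | 2.0 |

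The first three rows need only the stated SD and sample size. At 165 per arm the figures are slightly worse, for example 59% and 75% at 5 points.

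**What an interval would show.** The half-width of an unadjusted 95% interval is 1.960 × 2.845 = 5.6 points at 171 per arm. At 165 the SE is 26.31 × √(2/165) = 2.897 and the half-width is 5.7 points. Similarity shown by a 95% interval lying wholly inside ± margin, with no true difference and 80% power, needs 2[26.31 × (1.960 + 1.282)/margin]² per arm. The article gives no margin, so these are assumed values: 172 per arm for 9.21 points, 297 for 7 and 582 for 5.

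**Efficacy contrasts, for δ = 9.21.** Power is Φ(δ/SE − c).

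| Evaluable per arm | T = 3 | T = 2 |
|---|---|---|
| 171 | 80.0% | 84.0% |
| 165 | 78.4% | 82.6% |

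Reaching 80% with T = 2 takes 156 per arm in place of 171.

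**The case against.** **T = 3 may be conventional.** Three arms give three pairwise comparisons, and the Discussion uses the 2 versus 4 week contrast to choose a duration. Declaring one duration better is a claim of a difference, and such a test belongs in the family. This stands, and the remedy must allow for it. It conflicts, however, with hypothesis 1 as worded. Recruitment does not itemise the three comparisons, so the inclusion of hypothesis 1 is an inference, though the three hypotheses and the three pairs both point to it.

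**The correction is not the root of the problem.** This also stands. With no adjustment at all, a true 5-point difference would be missed 58% of the time. Taking hypothesis 1 out of the family would not turn non-significance into evidence of similarity.

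**Stronger readings that the article does not support.**
- A reader might infer that T = 3 always doubles the error on hypothesis 1. It does so only near the back-solved 9.2 points; at 3 to 7 points the ratio is 1.1 to 1.5.
- A reader might infer that T = 3 leaves the efficacy tests short of power. It does not: 171 was calculated with T = 3 and delivers 80%. The 78.4% at 165 comes from multiplying by 1.2 where dividing by 0.8 would give 214, which is a separate matter.
- A reader might infer that including hypothesis 1 is costly under any multiplicity procedure. With three arms, unadjusted pairwise tests made only after a significant overall ANOVA hold the family-wise error at 5% with all three pairs included. In a simulation at 165 per arm with both platform arms 9.21 points above control, each efficacy contrast had 86.3% power. The cost belongs to plain Bonferroni.

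**Conclusion.** The point holds in a limited form. The main fault is the decision rule for hypothesis 1, under which a prediction of no difference can be supported only by a non-significant difference test. The Bonferroni divisor of 3 aggravates this, adding 9 to 17 percentage points to the chance of false support for true differences between 3 and 9.2 points at 171 per arm. For the efficacy contrasts the effect is modest, about 4 points of power or 15 participants per arm, and the planned sample size already pays for it.

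The conclusion rests on three assumptions: that T = 3 counts the 2 versus 4 week comparison, that non-significance is the intended support for hypothesis 1, and that the SD is 26.31. Figures at 9.2 points and all power figures rest also on the back-solved difference. The calculations concern the preparedness score only. The point deserves correction because the duration question is one of the trial's stated purposes and the change needs no more participants.

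**What to change.** 1. In Study design and in the analysis section, stop drawing a conclusion of no difference from a non-significant test. Report the 2 versus 4 week difference in preparedness score with an unadjusted 95% interval (expected half-width 5.6 to 5.7 points), and claim similarity only if the interval lies within a margin fixed and justified in advance. Check the margin against the sample size: 171 per arm gives about 80% power for a margin near 9.2 points and too little for 7 or 5.
2. Reconcile Study design with the Intervention design section and the Discussion on whether this comparison predicts similarity, explores duration, or tests which duration is better.
3. Let the divisor follow from that decision. If the comparison is not a confirmatory difference test, use T = 2 for the two platform-versus-control contrasts on the primary outcome (two-sided 0.025 each), with power restated as about 84% at 171 or 83% at 165 per arm for a 9.2-point difference. If the sponsor wants to claim that one duration is better, keep that test in the family with T = 3.
4. Name the family in the Bonferroni sentence, and state the difference between means used for 171.

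The cost is wording only, with no added participants unless a margin tighter than about 9 points is chosen. The downside of T = 2 is that any difference found between 2 and 4 weeks would be exploratory, outside the family-wise 5%.

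### The 20% attrition allowance multiplies 171 by 1.2 instead of dividing by 0.8, so 206 per arm falls slightly short of the stated 80% power (minor)

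*Protocol article*

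**What the plan says.** The sample size calculation is in the Recruitment section of the protocol article and is tied to the primary outcome, the emergency preparedness score. It prints a formula for pairwise comparison of means with a Bonferroni-type critical value and lists these inputs: "The significance level of the test is α = 0.05", "the test power is 1-β = 0.8", "standard deviation is = 26.31" and "the number of comparisons to be made is T = 3". The result before any allowance for loss is given as: "Calculator software (Power and Sample Size) was used to calculate the initial sample size N1 = 171". The allowance follows: "Considering the attrition rate of 20%, the sample size of each group was increased to 206". Three arms of 206 give the stated total of 618.

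The section on randomization and allocation concealment carries these numbers into practice, with 618 random numbers and 206 envelopes per group. The article does not write out how 171 became 206.

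**The concern.** An attrition rate is the share of enrolled participants who are lost. If 20% are lost, 80% remain, so the number to enrol is the number needed divided by 0.8. Adding 20% of the number needed gives a smaller figure, because the loss is later taken from the larger enrolled number. The stated 206 is what the second operation gives.

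If so, three design figures conflict: 80% power (which needs 171 evaluable per arm), 20% attrition, and 618 enrolled. A reader who relies on the paragraph would believe that the trial keeps 80% power at the planned loss, when it falls a little below. The loss assumption is not idle here: follow-up runs to six months after the intervention, and the Limitations section names loss of participants during long follow-up as a risk.

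**Working it through.** **Inputs, all from the Recruitment section:** overall alpha 0.05; power 0.80; SD 26.31; T = 3 comparisons; 171 per arm before attrition; attrition 20%; 206 per arm and 618 in total after it. Equal allocation is confirmed by the 206 envelopes per group.

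**1. Reproduce the plan's figure.**
- Needed number x (1 + rate): 171 x 1.2 = 205.2, rounded up to 206. This matches exactly.
- Needed number / (1 - rate): 171/0.8 = 213.75, rounded up to 214. This does not match; the gap is 8 per arm, too large for rounding.

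**2. What 20% attrition requires.** 214 per arm, 3 x 214 = 642 in total. Check: 214 x 0.8 = 171.2. Compared with the plan, that is 8 more per arm and 24 more in total.

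**3. What 206 per arm delivers.**
- Remaining after 20% loss: 206 x 0.8 = 164.8, about 165 and about 6 below 171.
- Largest loss that still leaves 171: 1 - 171/206 = 0.170, so 17.0%.

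**4. The difference implied by 171.** The visible text gives no value for the difference in means, so it is solved from the plan's own formula, on the assumption that 171 gives exactly 80% power:
- z(1 - 0.05/6) = 2.394 and z(0.8) = 0.842; the sum is 3.2356.
- Difference = 26.31 x 3.2356 x sqrt(2/171) = 9.21 points, or 0.350 SD.

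**5. Power at the reduced number.** With 164.8 per arm:
- z = 9.206 / (26.31 x sqrt(2/164.8)) = 3.176.
- Power = Phi(3.176 - 2.394) = Phi(0.782) = 0.783. The second tail in the plan's formula is negligible.

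The SD and the difference cancel in this step: z is 3.2356 x sqrt(164.8/171) = 3.176. The result therefore rests on 171 being the number that gives 80% power, not on the value 9.2 as such.

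**6. Sensitivity.**

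| Variant | Evaluable per arm | Power |
|---|---|---|
| T = 3, 171 gives exactly 80% | 164 to 165 | 78.1% to 78.4% |
| T = 3, 171 rounded up from just over 170 | 164 to 165 | 78.3% to 78.6% |
| Alpha 0.05 without adjustment | 164 to 164.8 | 78.3% to 78.5% |

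The shortfall from 80% is about 1.4 to 1.9 percentage points throughout.

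**7. The same gap as a detectable difference.** sqrt(171/164.8) = 1.019, so the difference detectable with 80% power rises from 9.21 to about 9.38 points, that is by 0.17 points. The questionnaire has 53 items scored 1 to 5, so totals run from 53 to 265.

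**The case against.** The strongest reply is that the slip does not matter. A rise of 0.17 points in the detectable difference is trivial on this scale. An SD of 26.80 in place of 26.31 would cost the same power, and both the SD and the 20% loss are planning guesses. At 17% attrition or less there is no shortfall. This stands as an argument about severity. It does not make the stated figures consistent with one another.

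A second reply is that the analysis will be by intention to treat, so everyone randomized counts. The Data management and statistical analysis section does say this. But a participant lost to follow-up provides no later score. Imputation could keep that person in the analysis set without supplying the observation, and the allowance exists to keep 171 observed per arm.

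Three stronger readings are tempting and should not be drawn.
- A reader might infer that the trial is materially underpowered. Less than 2 percentage points does not support that.
- A reader might infer that the sponsor never fixed a difference to detect. The text does not allow that conclusion. The formula contains the difference, and software returned 171, so some value was used. The paragraph has also visibly lost inline symbols in text extraction, as in "standard deviation is = 26.31", where the symbol for the SD is gone. A value may have been lost in the same way, or may stand in the full protocol.
- A reader might infer that 618 can be defended by taking the two-week versus four-week comparison out of the Bonferroni family. That comparison is the first of the three hypotheses under Study design, and the Discussion relies on it to find the optimal duration. T = 3 fits those three comparisons. Removing one would change the multiplicity plan and would leave the attrition arithmetic uncorrected.

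**Conclusion.** The point holds as a minor arithmetic error. The allowance was computed as 171 x 1.2 where 171/0.8 was needed, giving 206 per arm instead of 214 and 618 instead of 642. At the plan's own 20% attrition, about 165 per arm remain and power per comparison is about 78%, not 80%.

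The counts (206, 214, 165 and the 17% limit) rest only on figures in the document. The 78% rests on one assumption: that 171 evaluable per arm gives 80% power, equivalent to a difference of about 9.2 points (0.35 SD) with SD 26.31 and T = 3. The 9.2 is a back-calculation and should not be taken as the sponsor's design value. No analysis or hypothesis changes.

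**What to change.** Keep 618 and correct the sentence on attrition in the Recruitment section, for example:

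> With 206 participants enrolled per arm (618 in total), at least 171 per arm remain evaluable if attrition does not exceed 17%. At 20% attrition about 165 per arm remain, and power per comparison is about 78% for a difference of [the sponsor's planning value] points.

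The sponsor should insert the difference it actually used and confirm the power figure against it; 9.2 points should not be copied in from this review. The cost is a change of wording. No participants are added, and the random sequence and envelopes stay as they are, which is the practical route because enrolment began in July 2022. If the sponsor wants to keep both the 80% power and the 20% attrition as stated, the alternative is 214 per arm (642 in total), at the cost of 24 more participants and an extended allocation list.

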#### Randomization and allocation concealment

To reduce selection bias, randomization and allocation concealment are essential. To achieve randomization, there are the following steps: 1) Sequence numbers are drawn up for 618 participants; 2) 618 random numbers are randomly generated by computer; 3) 618 random numbers are finally distributed to 618 participants. Opaque envelopes are used to allocation concealment. In each of the 618 envelopes, each will contain a note with the words “The People’s War Against Pandemic intervention group 1” or “The People’s War Against Pandemic intervention group 2” or “Control group”(206 envelopes per group). Participants will randomly select an envelope in the order of random number and be assigned to the corresponding group according to the information in the envelope. The grouping information is saved by a third party. Unlinding is permissible when participants exit the research or statistical analysis is completed.

### Outcomes and data collection

The primary outcome is emergency preparedness of public for MEIDs. The secondary outcome is prevention and control knowledge of MEIDs. The assessment of intervention group 1 will be conducted at baseline, week one and two of the intervention, and 1, 3, 6 months after the intervention. Assessment of the intervention group 2 will be conducted at baseline, week 1, 2, 3, 4 of intervention, and 1, 3, 6 months after the intervention. Assessment of the control group will be conducted at baseline, week one and two of the intervention, and 1, 3, 6 months after the intervention. In addition, participants' evaluation of the virtual interactive training system will be assessed at the completion of the intervention. Study schedule of enrolment, interventions, and assessments is shown in the Fig. 3.

